### Aim #4: design and create a digital toolkit for other ICUs to identify implementation determinants, customize an OR to ICU handoff protocol, and select appropriate implementation strategies

Using the lessons learned from customizing the HATRICC protocol and selecting and deploying various implementation strategies, we will create a digital toolkit for public use. A toolkit is a collection of information, resources, and details about how to implement a given process [62]. The creation of implementation toolkits is not uncommon [62–64], as they may help narrow the gap between implementation and practice. The web-based HATRICC-US toolkit will make the study findings usable by allowing users to input contextual factors, design and adapt process maps, select implementation strategies, and download customizable versions of OR to ICU handoff protocols. The goal of this toolkit is to provide smaller, less well-resourced, and community-based settings the opportunity to replicate aims 1 and 2 of the HATRICC-US study in silico, facilitating the uptake and use of standardized OR to ICU handoffs.

The HATRICC-US toolkit will be created using human-centered design (HCD), which incorporates the perspectives of current and potential stakeholders in creation of the toolkit to optimize usability [49, 65].

### Sample size calculation

Sample size will vary by aim and approach. In general, qualitative data will be sampled until meaning saturation [66] is reached. For our co-primary quantitative outcomes, additional detail is provided below. We assume a type 1 error rate of 0.05 despite having co-primary outcomes, as the implementation outcome of fidelity and the effectiveness outcome of new-onset organ failure are drawn from different analytic samples (handoff vs. ICU, respectively).

Co-primary outcome #1—Fidelity (patient handoff-level outcome): We selected a sample size sufficient to confer at least 90% power to detect a 1-point increase in fidelity; this corresponds to 15 handoffs per ICU per month, or 3–4 handoffs per ICU per week. The total sample for this outcome is expected to be between 1920 and 2880 handoffs.

Co-primary outcome #2—Number of new-onset organ failures (ICU-level outcome): The number of eligible patients is fixed given the focus on ICU-level outcomes. We determined that at the expected available sample size, we achieved > 90% power to observe at least a 10% relative decline (our threshold for the minimally important clinical difference [67]) in the number of new-onset organ failure cases, from 1.5 cases per 100 patients to 1.35 cases per 100 patients. The total expected patient count for this ICU-level outcome is between 20,000 and 30,000 patients.

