In the Handoffs and Transitions in Critical Care (HATRICC) study, we studied the effectiveness and implementation of a standardized OR to ICU handoff protocol in mixed surgical ICUs [12–14, 21–23]. From an implementation perspective, barriers to achieving a standardized handoff process included unclear expectations, time pressure, and confusion about other providers’ needs [13]. Multiple stakeholder perspectives provided important contextual information used as inputs for the selection of implementation strategies to support the uptake and use of a new handoff protocol. We combined findings from the contextual inquiry, a synthesis of pre-existing literature, and in situ simulation to design a standardized handoff protocol. We showed that handoffs adhering to this protocol improved information exchange and had high clinician acceptability [13, 14]. Although this work was one of the larger studies of OR to ICU handoffs [20], it was effectively a pilot study limited in detecting associations between the intervention and clinical outcomes due to its modest sample size (*n* = 165 observations). Implementation lessons were similarly limited given the scope of the study, which was based in two ICUs in two hospitals in a single health system.

The present study builds on this prior work by scaling up to multiple academic health systems. This fully powered trial will allow us to test confirmatory hypotheses and extend our understanding to more health systems. We will therefore be able to characterize implementation determinants in multiple centers and will be able to test relationships between the intervention and patient outcomes. This study may also allow us to characterize implementation determinants in critical care more broadly. The HATRICC handoff protocol serves as an exemplar use case for testing implementation in critical care, as OR-to-ICU handoffs are common (> 10 handoffs per ICU per week), occur in a known location, and are a complex interaction requiring engagement from multiple care team members.

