### Study team and governance

The study team is a multidisciplinary, multiprofessional group of researchers and subject matter experts with backgrounds in implementation science, human factors engineering, systems engineering, change management, organizational theory, biostatistics, mixed methods research, anesthesiology, critical care, nursing, and surgery. There are no patients or caregivers as part of the study team, as the process of interest for the current study concerns technical aspects of care that are in many ways invisible to patients and caregivers. The core research team consists of an overall Principal Investigator (PI), four additional site PIs, faculty-level collaborators, and research staff (Fig. 2). Each “site” is an academic health system contributing 1–4 ICUs to the overall study, for a total of 12 ICUs. Each ICU represents a cluster whose implementation start time will be randomized.

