### Aim #3: test the effectiveness of tailored, multifaceted, multilevel implementation strategies

After 4–6 weeks of baseline data collection in all ICUs, each ICU will implement the new HATRICC protocol using the implementation strategies selected in aim 2. We shall use a stepped wedge [52] approach to implementation start time, with each new “step” occurring 6–8 weeks after the prior step. The step duration was selected to balance the goal of clearly demarcating the change to a new handoff procedure and allowing for “wash in” (favors a longer step) with the goal of completing the implementation efforts in all ICUs with sufficient time to collect at least 12 months of sustainment data (favors a shorter step). This stepped wedge approach will enable each ICU to serve as its own control. Implementation start times will be randomized, though in hospitals with more than one ICU participating, ICU start times will be sequential. All ICUs will collect data for the duration of the study, estimated to be 4 years.

Aim 3 measures are shown in Table 1. The co-primary outcomes are fidelity (implementation outcome at the level of each handoff observation) and cases of new onset organ failure (effectiveness outcome at the level of the ICU).

**Table 1 Tab1:** HATRICC-US outcome measures

Outcome (type)	Rationale	Unit of analysis and approach to measurement	Frequency and timing of measurement
Co-primary outcomes			
Fidelity (Imp)	Fidelity is a necessary precursor to effectiveness	Handoff-level; observations by site-based staff, count on a 10-point scale (quant), field notes (qual)	Monthly, Years 2-5
New-onset organ failure (Eff)	Per-protocol handoffs enable clinicians to follow expected care practices and to anticipate and avoid postoperative deterioration	ICU-level; composite measure of AHRQ Patient Safety Indicators (PSIs) [53] that reflect organ failure (quant)	Monthly, Years 2-5
Secondary outcomes			
Feasibility (Imp) Acceptability (Imp) Appropriateness (Imp)	These “early” implementation outcomes will influence subsequent fidelity and will help in the interpretation of fidelity findings	Clinician- and ICU-level; AIM [54], FIM [54], IAM [54] (quant); site visit findings (qual)	3 times: Year 1; within 2 months of implementation (Years 2-3); within 2 months of sustainment start (Years 4–5)
Sustainment (Imp)	Sustainment is the ultimate goal of the implementation effort	Handoff-level; characterized as fidelity over time (quant)	Monthly, Years 4–5

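### The stated power above 90% for a 10% relative fall in organ failure cannot be obtained from the article's own rates and patient count; an ideal comparison gives about 14–19% two-sided.

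*Protocol article*

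**What the plan says.** The section Sample size calculation gives all the inputs in one place. On significance level: "We assume a type 1 error rate of 0.05 despite having co-primary outcomes". On power for organ failure: "we achieved > 90% power to observe at least a 10% relative decline", which it expresses as a change "from 1.5 cases per 100 patients to 1.35 cases per 100 patients". It calls this 10% decline its threshold for the smallest clinically important change. On size: "The total expected patient count for this ICU-level outcome is between 20,000 and 30,000 patients". It adds that the number of eligible patients is fixed. Sidedness, the intracluster correlation or dispersion, and the power method are not stated.

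The Background draws on this calculation: "This fully powered trial will allow us to test confirmatory hypotheses", including tests of how the intervention relates to patient outcomes.

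The design comes from three other places. Study team and governance: "Each ICU represents a cluster whose implementation start time will be randomized", with 12 ICUs. Aim #3: the intervention follows "After 4–6 weeks of baseline data collection in all ICUs", in steps 6 to 8 weeks apart, with all ICUs collecting data for about 4 years. Data analysis: a mixed-effects negative binomial model with random ICU effects and fixed time effects.

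**The concern.** A difference of 0.15 percentage points on a base of 1.5% is very small, and 300 to 450 events in total cannot resolve it with high power. The rates, the total and the power stand side by side, so the conflict does not depend on any unseen method.

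The outcome is co-primary and the 10% decline is the authors' own threshold of importance. If true power is below 20%, a non-significant result is the likely outcome even when the handoff protocol achieves exactly that decline. A reader who trusts the stated power would take such a result as evidence that no important benefit exists.

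**Working it through.** **Inputs.** Control rate p1 = 0.015 and intervention rate p2 = 0.0135; total N = 20,000 to 30,000; alpha = 0.05 (all from Sample size calculation). Two-sided testing is assumed, and one-sided is also shown.

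**Events.** 0.015 × 20,000 = 300 and 0.015 × 30,000 = 450 if every patient had the control rate.

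**Attempt to reproduce the power above 90%.** Ideal case: 1:1, no clustering, no time effects. With n = N/2 per condition and p̄ = 0.01425:

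- SE = √[2 p̄(1 − p̄)/n], which is 0.001676 at N = 20,000 and 0.001369 at N = 30,000. The unpooled SE is the same to this accuracy.
- Power = Φ(0.0015/SE − 1.96).
- N = 20,000: Φ(0.895 − 1.96) = Φ(−1.065) = 14.3%.
- N = 30,000: Φ(1.096 − 1.96) = Φ(−0.864) = 19.4%.
- One-sided (1.645 in place of 1.96): 22.7% and 29.2%.

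Counting rejections in the wrong direction as well adds at most 0.2 percentage points to the two-sided figures.

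**Other readings tried.**

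| Reading | Two-sided | One-sided |
|---|---|---|
| 1:1, N as total | 14.3–19.4% | 22.7–29.2% |
| N taken as per arm (40,000–60,000 in total) | 24–34% | 35–46% |
| One-sample test against a fixed 1.5%, every patient on intervention | 41–57% | 54–70% |

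None reaches 90%. The second contradicts the article's own use of a total, and the third discards the control data.

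**Sample size for 90% power (two-sided, 1:1).** n per arm = [1.96 √(2 p̄(1 − p̄)) + 1.2816 √(p1(1 − p1) + p2(1 − p2))]² / 0.0015² = (0.3285 + 0.2148)² / 0.00000225 ≈ 131,200, or about 262,400 in total. Against 30,000 and 20,000 that is 8.7 and 13.1 times the expected count. One-sided, the total is about 213,900.

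**Detectable decline.** Solving the same power formula for p2 at 90% gives a relative decline of about 34% at N = 20,000 and 28% at N = 30,000.

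**Stepped-wedge model.** The article does not give the number of sequences, the accrual pattern, the form of the time effect or the between-ICU variance, so this part is a range under assumptions:

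- 12 ICUs in 4 to 12 sequences; baseline 4 weeks with 6-week steps, or 6 weeks with 8-week steps; 208 weeks; even accrual.
- Poisson counts (no overdispersion), categorical period effects, random ICU intercept with SD 0 to 5 on the log scale.
- SE of the log rate ratio from the generalised least squares information matrix. The target is |ln 0.9| = 0.105.
- Power = Φ(0.105/SE − 1.96) + Φ(−0.105/SE − 1.96).

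Most favourable case (N = 30,000, 12 sequences, 6/8-week schedule, ICU SD 0): SE 0.175, power 9.2%. Least favourable (N = 20,000, 4 sequences, 4/6-week schedule, large ICU SD): SE 0.456, power 5.6%. The range is therefore roughly 6–9%. Linear instead of categorical time gives about 7–11%. Placing all patients inside the roll-out gives about 9–14% for ICU SD 0 to 0.3. Negative binomial overdispersion would lower all of these.

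**The case against.** The strongest defence is that this is a condensed article: the power method may be in a fuller protocol or analysis plan, and its absence here is no fault. That is right about the method, but it does not help the figure. Clustering, time effects and overdispersion, the features one would expect a fuller calculation to add, reduce power here, and none of the simpler readings tried comes near 90%.

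Three further points limit what can be claimed, and they stand:

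- A reader might take 14–19% as an absolute ceiling. It is the ideal figure for a two-sided test only. The article does not state sidedness, and one-sided the ideal figure is 23–29%.
- A reader might want one stepped-wedge figure, say 7–8%. The article does not fix the layout that this needs. The Discussion says the last ICU will have just over a year of sustainment data, which could mean a longer roll-out than 12 consecutive short steps. Stretching roll-out to week 152 still gives only about 9% at most, but the result has to be reported as a range.
- A reader might infer that patients treated after every ICU has switched contribute almost nothing once time is fitted. Under a model with freely estimated ICU effects and period effects this is not so. With 12 steps and N = 20,000, dropping them raises the SE from 0.273 to 0.355 (4/6-week schedule) or from 0.246 to 0.306 (6/8-week). They carry 1 − (0.273/0.355)² = 41% or 1 − (0.246/0.306)² = 35% of the information. The inference holds only when between-ICU variance is small.

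It is also tempting to explain the discrepancy by a slipped decimal in the base rate. Nothing in the article supports that explanation over any other.

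Finally, the Background's description of the trial as fully powered covers fidelity too, and this point does not dispute the power for fidelity.

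**Conclusion.** The power statement for organ failure is wrong as written. The printed rates and total give about 14–19% power two-sided (23–29% one-sided) in an ideal unclustered 1:1 comparison, against a stated figure above 90%. That conclusion needs only the article's own inputs.

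The lower range under the declared design, roughly 6–9% two-sided, rests on the layout assumptions listed with the calculation. It shows the direction and rough size of the further loss, not an exact value. The claim that the trial is fully powered for confirmatory testing is not supported for organ failure. The error affects how the result will be interpreted; recruitment is unaffected, since the article treats the number of patients as fixed.

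**What to change.** Recompute the power for organ failure under the actual stepped-wedge layout and replace the sentence. State sidedness, the number of sequences, the accrual pattern, the form of the time effect, and the between-ICU variance and overdispersion assumed. Beside it, give the relative decline that can be detected with 90% power.

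If the base rate or the patient count is misstated, correct it and show that the corrected inputs reproduce the claimed power.

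If the figures stand, limit the fully powered and confirmatory wording in the Background so that it no longer covers organ failure. State in advance that a non-significant result does not exclude the 10% decline named as important, and report the rate ratio with its confidence interval.

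The cost is rewriting the sample-size paragraph and one Background sentence. No more patients and no change of design are needed; the drawback is a less favourable stated power.

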### Data analysis

To analyze qualitative data, we shall use a mix of inductive and deductive approaches. The inductive approach will use applied thematic analysis [68], selected because we have a process-oriented goal—applying findings to implementation strategy selection. For our analysis, qualitative data will be coded in cycles by trained research assistants. The first cycle of coding will enable generation of a codebook grounded in the data. During successive coding cycles, we will refine the codebook to reflect emerging themes and recode data using a constant comparative approach [69]. The coding team will meet to refine the codebook and to explore emerging themes. For the deductive approach, we will compare our codebook to relevant constructs from the TICD Checklist [38] to look for similarities and differences. We will also examine how different levels of the social ecologic model [40] manifest themselves in the data. This mix of inductive and deductive approaches will allow us to discern findings that may not be reflected in the published literature while still allowing us to translate our findings to established behavior change theories. We will use the qualitative data analysis program NVivo (QSR International, Doncaster, Australia) to manage qualitative data.

The quantitative data from aim 1 are descriptive. We will therefore use descriptive statistics to summarize findings from observations and surveys with stakeholders during this contextual inquiry phase. We will develop visual and mathematical summaries of overlap and concordance, such as Venn diagrams, influence diagrams, and clustering analyses to facilitate understanding of our findings and to communicate these findings effectively with local implementation teams and other stakeholders [70, 71].

The aim 3 primary analysis will utilize a mixed-effects negative binomial regression model with random effects for ICU site and fixed effects for time to account for the stepped-wedge cluster randomized design. Based on the distribution of the data, we may perform sensitivity analyses using linear regression (for fidelity) and logistic regression (for new-onset organ failure).

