**Fig. 4 Fig4:**
[figure not shown]
Exemplar process map of OR-to-ICU handoffs

After process mapping, we will conduct another set of interviews and focus group discussions to identify handoff protocol implementation determinants (i.e., barriers to and facilitators of implementation) in each ICU. Clinicians representing the key roles in OR to ICU handoffs (surgeon, anesthesia provider, nurse, ICU ordering provider) will participate in mixed-role focus groups facilitated by trained members of the core study team. Participants will provide multiple perspectives on post-surgical handoffs, protocols, and clinical quality improvement initiatives. Given their smaller number, clinical leaders and administrators will participate in semi-structured interviews about their multiple perspectives on ICU protocols and then OR to ICU protocols specifically. Both focus group and interview scripts were designed for this study and informed by EPIS [37] and the TICD Checklist [38]; research team members and clinician subject matter experts selected relevant determinants from these frameworks. Participants will be recruited using purposive and snowball sampling [44]. Within each site, recruitment will be stratified by role, gender, and experience level.

Observations will be conducted by on site staff and will be directed by site PIs. Trained observers will use a common report form to capture details about clinical topics discussed during OR to ICU handoffs, clinicians present during each handoff, and fidelity, defined as adherence to the ten elements of the originally published HATRICC protocol (i.e., introduction of team members upon patient arrival, patient stabilization, transfer of patient to in-room monitors, huddle of handoff team members, surgery report, anesthesia report, ICU provider synthesis, team physical exam of patient, exchange of contact information, question asking period (Fig. 1b)) [14]. We expect fidelity at baseline to be greater than zero, as some of the protocol elements are commonly conducted even in the absence of a protocol.

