Affordability (Cost; Imp)	Implementation cost is an important consideration for transferability of study findings	ICU-level; accounting-based cost analysis as described by Hoeft et al. [55] (quant)	Within 2 months of implementation; within 2 months of sustainment start
Teamwork (Eff) Professionalism (Eff)	Strong teamwork and professionalism are expected to result from protocol use	Handoff-level; field notes from trained site-based staff (qual)	Quarterly, Years 2–5
Clinician satisfaction (Eff)	Clinician satisfaction is an early indicator of effectiveness	Clinician-level; surveys (quant); site visit findings (qual)	Annually, Years 1–5
Clinician workload (Eff)	Workload influences clinicians’ EBP use; fidelity is likelier if workload is unchanged or lower	Clinician-level; NASA Task Load Index [45] (quant); field notes, site visit findings (qual)	Quarterly, Years 2–5
Information omissions (Eff)	Per-protocol handoffs will show fewer information omissions	Handoff-level; direct observations* by trained site-based staff (quant)	Monthly, Years 2–5
Adverse events (Eff)	Per-protocol handoffs include enable the prevention of adverse events by promoting shared team understanding of patients’ care	ICU-level; composite measure based on 10 routinely collected measures of care (AHRQ PSI 90 [56])	Quarterly, Years 2–5

*AHRQ* Agency for Healthcare Research and Quality, *AIM* Acceptability of Intervention Measure [54], *Eff* effectiveness outcome, *FIM* feasibility of intervention measure [54], *IAM* intervention appropriateness measure [54], *ICU* intensive care unit, *Imp* implementation outcome, *PSI* patient safety indicator, *qual* qualitative measure, *quant* quantitative measure

We selected fidelity as our primary implementation outcome based on our original study, in which increased effectiveness of the HATRICC protocol, as measured by information completeness, was observed with increasing fidelity to the process [14]. Though the concept of handoff fidelity could be defined in different ways given that the OR to ICU handoff is a complex sociotechnical work system, we define fidelity as a count of adherence to the ten steps defined in the original process.

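### Fidelity is a count of ten steps, but its primary model is a negative binomial, which has no ceiling at 10 and cannot represent variance below the mean

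*Protocol article*

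**What the plan says.** The Data analysis section names one primary model for aim 3: "The aim 3 primary analysis will utilize a mixed-effects negative binomial regression model", "with random effects for ICU site and fixed effects for time". Aim #3 and Table 1 list two co-primary outcomes, handoff-level fidelity and ICU-level new-onset organ failure, and no separate primary model is named for either. Linear regression enters only conditionally, depending on how the data are distributed: "we may perform sensitivity analyses using linear regression (for fidelity").

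Table 1 describes fidelity as a "count on a 10-point scale (quant"), and the text after the table adds that "we define fidelity as a count of adherence to the ten steps defined in the original process". On starting levels, the Aim #1 section says only: "We expect fidelity at baseline to be greater than zero", because some steps are commonly done without a protocol. The Sample size calculation section sets the target in absolute points: "We selected a sample size sufficient to confer at least 90% power to detect a 1-point increase in fidelity".

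The article gives no standard deviation, baseline mean, correlation between steps, link function, standard-error method or conversion of the model estimate to points.

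**The concern.** A negative binomial suits open-ended event counts with extra-Poisson variation, which is a reasonable description of organ-failure cases. Fidelity differs in two ways. It stops at 10, and its variance relative to its mean falls as adherence rises. A negative binomial can add variance to a Poisson but cannot remove any, and the ICU random effect does not help, because it too only adds variance. When scores vary less than a Poisson with the same mean, the dispersion estimate goes to its zero boundary and the model reports Poisson standard errors.

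At stake are the width of the confidence interval and the calibration of the p-value for a co-primary outcome. There is also a smaller matter of scale: the usual log-link estimate is a ratio, whereas the trial was planned around a difference of one point.

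**Working it through.** **Inputs from the article.** 12 ICUs; 15 handoffs per ICU per month; 1920 to 2880 handoffs; fidelity from 0 to 10; target +1 point; power at least 90%; type 1 error 0.05.

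**Assumptions.** Log link, two-sided test, model-based standard errors, baseline means of 4 to 8 points, and a common correlation ρ between steps within a handoff of 0, 0.1 or 0.3. For power: SD 1.5 to 3, intracluster correlation 0.05 to 0.2, and 4, 6 or 12 sequences.

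**1. The plan's own figures.** 15 × 12 = 180 handoffs per month, so 1920 is 10.7 months and 2880 is 16.0 months. 15 × 12/52 = 3.46 per week, which agrees with the stated 3–4. The standard stepped-wedge variance formula (Hussey and Hughes) gives 98.9% to 100% power for one point over the assumed range. The claim of at least 90% is therefore consistent, although it cannot be reproduced as a single value.

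**2. The ceiling.** A 0–10 score with mean m has variance at most m(10 − m), which is below m whenever m > 9. Near full adherence, no step correlation can make the negative binomial variance correct. At the Poisson limit the model puts about 4%, 10% and 18% of handoffs above 10 steps at means 6, 7 and 8.

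**3. Standard-error inflation.** With p = mean/10, the score variance is 10p(1 − p)(1 + 9ρ) and the Poisson variance is 10p. The reported SE divided by the true SE is

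√{1 / [(1 − p)(1 + 9ρ)]}, where this exceeds 1.

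| Mean | ρ = 0 | ρ = 0.1 | ρ = 0.3 |
|---|---|---|---|
| 5 | √(1/0.5) = 1.41 | √(1/0.95) = 1.03 | none (variance above mean) |
| 7 | √(1/0.3) = 1.83 | √(1/0.57) = 1.32 | none (variance above mean) |
| 8 | √(1/0.2) = 2.24 | √(1/0.38) = 1.62 | √(1/0.74) = 1.16 |

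Variance reaches the mean at ρ = [1/(1 − p) − 1]/9, which is 0.074, 0.111, 0.167, 0.259 and 0.444 at means 4, 5, 6, 7 and 8.

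**4. Unequal steps.** The formula assumes that all ten steps are equally likely, yet the article says some are already common. As an illustration, take three steps at 0.95, four at 0.40 and three at 0.18. The mean is 2.85 + 1.60 + 0.54 = 4.99 and the variance with independent steps is 0.143 + 0.960 + 0.443 = 1.55. The ratio of variance to mean is 0.31, against 0.50 for equal steps. SE inflation becomes 1.80 at ρ = 0 and 1.33 at ρ = 0.1.

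**5. Simulation.** 12 ICUs, 6 sequences, 2880 handoffs, 250 runs per scenario. ICU effects were fitted as fixed and the negative binomial dispersion was estimated by moments with a floor at zero, so this approximates the planned mixed model. Entries are reported SE / empirical SD and the null rejection rate of a nominal 5% test.

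| Baseline | ρ = 0 | ρ = 0.1 | ρ = 0.3 |
|---|---|---|---|
| 4 | 1.40; 1.2% | 1.01; 5.6% | 0.97; 6.4% |
| 6 | 1.50; 0.4% | 1.17; 2.0% | 1.05; 3.6% |
| 7 | 1.78; 0% | 1.35; 0% | 1.00; 6.4% |

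With a true +1 point at ρ = 0.3 the SE ratio was 0.91 to 0.96, so the inflation is gone and may reverse slightly. Power for +1 point was 99.6% to 100% in every negative binomial scenario. On the same data, linear regression rejected in 2.8% to 7.6% of null runs and estimated 0.96 to 1.00 points for a true 1.

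**6. Scale.** One point is a ratio of 4/3 = 1.33, 5/4 = 1.25, 7/6 = 1.17 or 9/8 = 1.125 from baselines 3, 4, 6 or 8. No single ratio corresponds to the planned target if ICUs start at different levels.

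**The case against.** The strongest reply is that the inflation rests on quantities the article does not give. Several steps (huddle, surgery report, anesthesia report, ICU synthesis, questions) plausibly occur together once the team gathers, so positive correlation is likely. Modest correlation is enough to remove the problem at low-to-middle means: at baseline 4 and ρ = 0.1 the simulated ratio is already 1.01. A baseline described only as above zero does not establish middle or high scores. This stands. A reader might infer that the model is certain to overstate its standard errors; the documents do not support that.

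A reader might also infer that fidelity variance falls steadily as scores rise. With equally likely steps it rises up to a mean of 5 and falls only above that; it is the ratio of variance to mean that falls throughout.

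It can also be said that the ratio scale is no obstacle, because a difference in points can be obtained by marginal standardisation, and that link, reporting scale and standard-error method belong in an analysis plan that is not shown. That largely stands, and it makes the scale issue minor.

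Finally, the article already allows for linear regression. This stands only in part: it is optional and a sensitivity analysis, so the primary model for fidelity does not change. The mismatch between that model and a count capped at 10 does not depend on any unstated figure.

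**Conclusion.** The negative binomial is a stated primary choice that fits fidelity badly: it has no ceiling and cannot represent variance below the mean. Model-based standard errors would probably be too large, by 1.4 to 2.2 times at means 5 to 8 with independent steps and 1.0 to 1.6 times at step correlation 0.1, with little or no inflation at means of 7 or below with correlation 0.3. These sizes rest on assumed step correlations and means, a log link and model-based standard errors.

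A reader might infer that the trial is underpowered for fidelity or exposed to material false-positive risk. Neither is shown. Where inflation occurs it is conservative, and power for one point stayed well above 90% in every scenario tried. The practical cost is an interval that is probably too wide for a co-primary outcome, and an effect whose usual form is a ratio when the target is one point. The change is worth making, but it is not critical to the trial's validity.

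**What to change.** For fidelity only, name one of these as the primary model before outcome data are examined:

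- a mixed binomial or beta-binomial model for steps done out of 10, with the marginal difference reported in points; or
- the linear mixed model on the 0–10 score, with robust or small-sample standard errors suited to 12 ICUs.

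Keep the random ICU effect and fixed time effects. Keep the negative binomial for organ-failure counts and, if wanted, as a sensitivity analysis for fidelity.

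The cost is analysis-plan wording: no new data are needed, and linear regression is already named. Each option has a small downside. The linear model does not respect the ceiling. The beta-binomial needs a marginalisation step, and it cannot go below binomial variance, so very unequal steps could still leave it somewhat conservative (in the illustration with independent steps, √(2.50/1.55) = 1.27, against 1.80 for the Poisson limit).
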